### 8.3.13 Neuropsychological assessment

#### *Cognitive performance*

To assess potential effect of the intervention on brain health, an insight in cognitive function is needed, for which we will be using components of the *Cambridge Neuropsychological Test Automated Battery* (CANTAB).(48) The CANTAB will be performed on CID 1 and 3 and will last approximately 45 minutes.

The CANTAB will focus on attention, psychomotor speed, executive function and memory. Before the tests, all participants will be familiarised with an example and receive instructions in Dutch by the investigator. All tests of the CANTAB are computerized and presented on a device with touch screen (iPad 2017). Data are instantly and safely recorded. The test will in fixed order, as described below:

- Attention and psychomotor speed
  - Motor Screening Task: provides a general assessment of whether sensorimotor deficits or lack of comprehension, will limit the collection of valid data from the participant. Duration: approximately 2 minutes.
  - Reaction Time: provides assessments of motor and mental response speeds, as well as measures of movement time, reaction time, response accuracy and impulsivity. Duration: approximately 3 minutes.
- Executive function
  - Multitasking Test: assesses the participant's ability to manage conflicting information provided by the direction of an arrow and its location on the screen and to ignore task-irrelevant information. Duration: approximately 8 minutes.
  - Spatial Span: assesses visuospatial working memory capacity. Duration: approximately 5 minutes.
  - Executive function
  - Delayed Matching to Sample: assesses both simultaneous visual matching ability and short-term visual recognition memory, for non-verbalisable patterns. Duration: approximately 7 minutes.
  - Paired Associates Learning: assesses visual memory and new learning. Duration: approximately 8 minutes.

#### *Wellbeing and stress*

To assess a participants impression of its own wellbeing and stress, two additional questionnaires will be filled in: the *RAND 36-item Short Form Health Survey* (SF-36)(49, 50) and the *Perceived Stress Scale 10* (PSS-10)(51, 52), respectively. Both surveys will be completed on or in the week prior to CID 1 and 3.

### 8.3.14 Dietary intervention

At the end of CID 2, participants receive the assigned intervention (potato-pectin fibre mixture or placebo), in a blinded manner to both the participant and original investigator. Participants will start using the dietary supplement the day after CID 2 and continue to do so for 84 consecutive days. The assigned supplement should be consumed thrice daily during breakfast, lunch and dinner. Along with the dietary supplement, all participants should consume a diet high in proteins (see below). This diet will be composed in collaboration with a dietician to provide a diet suitable to each individual's needs and taste. Furthermore, subjects are asked to consume  $\leq 1$  alcohol units/day, based on the national dietary guidelines.(53)

Additionally, all participants will follow a diet high in proteins alongside the dietary supplement, of which the exact composition will be discussed individually to establish a diet suited to the participants' needs and taste. The energy requirements for this diet will be estimated using indirect calorimetry. The diet will consist of 25 energy percentage (E%) protein mixture, 30E% fat and 45E% carbohydrate. Proteins will be 45-50% plant-based and 50-55% animal-based, to ensure a resemblance to the current western diet consisting of mainly animal-based proteins, while simultaneously acting on the currently shifting trend into more plant-based protein-rich components.

### 8.3.15 Procedure justification

The screening procedure is necessary to determine eligibility and safety of participation, requiring a thorough medical history questionnaire, blood sampling and measuring of anthropometrics. Therefore, the described measures in the screening and physical examination section are required.

Blood sampling and faecal sampling are necessary to analyze differences from baseline in metabolic and inflammatory (serum) markers and microbiome functioning and composition (primary and secondary outcomes). Blood samples will be drawn and faecal samples will be provided on multiple occasions during the intervention period to analyze relatively acute and long-term effects of the intervention. The required amounts as described earlier are therefore needed to be able to analyze these effects. Blood sampling will bring a small burden to participants (apart from the risks that are described elsewhere (8.3.3 and 13.1, 13.2), because sample drawing can be done using the already intravenously placed cannulas that are needed for other experiments.

The multisugar tests, bringing a relatively low burden to participants, is necessary to analyze gut permeability. The execution of this test (ingestion of a sugar mixture and urine collection) is a rather low burden on participants in relation to the valuable data this provides. The

collected urine can additionally be used to complement indirect calorimetry data to determine protein oxidation.

The DEXA scan is the least invasive way to obtain accurate data on body composition, which is needed to answer secondary objectives (changes in body composition). Instead of DEXA, an MRI could be performed, which is more burdensome for some participants, time-consuming, and costly.

The fMRI as proposed in this protocol is the only way to establish food reward-related brain activity and is therefore essential. Additionally, to measure neurocognitive functioning, the CANTAB, which is a widely used test battery to analyze these parameters, will be used. To analyze stress-related symptoms, which can hypothetically, also be improved by increasing carbohydrate fermentation, specific stress-analyzing questionnaires will be used. Different aspects of neurocognitive/psychological functioning need to be investigated to be able to address the effects of the intervention on brain health. By excluding one of these procedures, an incomplete insight will be provided on this aspect.

Tissue biopsies are needed to analyze specific intracellular pathways, signalling and oxidation, as well as cell size. Taking biopsies is the only possible way to analyze these markers to answer secondary objectives.

The hyperinsulinaemic-euglycemic is the gold standard to assess peripheral, hepatic and adipose tissue insulin sensitivity. It is an invasive procedure, but allows optimally for analyzing insulin sensitivity in different tissues, as well as for comparing data to available literature worldwide. Additionally, the indirect calorimetry, which is performed during the clamp and is of minor importance regarding invasiveness, combined with urinary nitrogen analysis, is the only mechanism to analyze oxidation of the different macronutrients correctly.

Multiple questionnaires will be used: they are needed to determine adherence to the prescribed diet and physical activity restrictions, as well as establish estimated baseline caloric intake and energy expenditure. To assess side-effects, the GSRS and BSS are the least invasive techniques available.

In general, all described procedures and tests are needed to answer the primary and secondary study objectives as stated in section 8.1.

#### **8.4 Withdrawal of individual subjects**

Subjects can leave the study at any time for any reason if they wish to do so without any consequences. The investigator can decide to withdraw a subject from the study for urgent medical reasons.

#### **8.4.1 Specific criteria for withdrawal**

Apart from the opportunity for the subject to leave the study at any moment, a participant will also be withdrawn from the study in case of any situation making continuing of the study unsafe. Also, if one of the exclusion criteria is met during the study, withdrawal will follow.

#### **8.5 Replacement of individual subjects after withdrawal**

If a participant withdraws from the study, an alternative candidate may be selected to meet earlier established sample size/power.

#### **8.6 Follow-up of subjects withdrawn from treatment**

If a participant withdraws from the study, no follow-up is needed, unless a medical reason occurs for further follow-up. If medical assistance is needed, this will be provided by the investigator, if this falls within his/her capabilities. If needed, the participant will be referred to the correct caregiver.

#### **8.7 Premature termination of the study**

In case Maastricht University, government agencies or the METC AZM/UM stop the study for unexpected reasons, the project will be terminated. Unexpected reasons include the safety of the participant, due to unexpected effects of the study products as well as a condition that make it impossible to continue the research such as another viral pandemic (i.e. worsening of the Covid-19 situation) that strongly limit personal contacts. In case of premature termination, the METC AZM/UM will be notified within 15 days.

## **9. SAFETY REPORTING**

### **9.1 Temporary halt for reasons of subject safety**

In accordance to section 10, subsection 4, of the WMO, the sponsor will suspend the study if there is sufficient ground that continuation of the study will jeopardise subject health or safety. The sponsor will notify the accredited METC without undue delay of a temporary halt including the reason for such an action. The study will be suspended pending a further positive decision by the accredited METC. The investigator will take care that all subjects are kept informed.

### **9.2 AEs, SAEs and SUSARs**

#### **9.2.1 Adverse events (AEs)**

Adverse events are defined as any undesirable experience occurring to a subject during the study, whether or not considered related to the investigational product. All adverse events reported spontaneously by the subject or observed by the investigator or his staff will be recorded.

#### **9.2.2 Serious adverse events (SAEs)**

A serious adverse event is any untoward medical occurrence or effect that

- results in death;
- is life threatening (at the time of the event);
- requires hospitalisation or prolongation of existing inpatients' hospitalisation;
- results in persistent or significant disability or incapacity;
- is a congenital anomaly or birth defect; or
- any other important medical event that did not result in any of the outcomes listed above due to medical or surgical intervention but could have been based upon appropriate judgement by the investigator.

An elective hospital admission will not be considered as a serious adverse event.

A medical doctor will be present or reachable by phone/pager at all times during a CID. If necessary, a doctor will provide medical assistance or a referral to the MUMC+ will be carried out. In life-threatening emergencies, regular national guidelines will always be followed.

The investigator will report all SAEs to the sponsor without undue delay after obtaining knowledge of the events.

The sponsor will report the SAEs through the web portal *ToetsingOnline* to the accredited METC that approved the protocol, within 7 days of first knowledge for SAEs that result in death or are life threatening followed by a period of maximum of 8 days to complete the initial preliminary report. All other SAEs will be reported within a period of maximum 15 days after the sponsor has first knowledge of the serious adverse events.

#### **9.2.3 Suspected unexpected serious adverse reactions (SUSARs)**

Not applicable

#### **9.3 Annual safety report**

Not applicable

#### **9.4 Follow-up of adverse events**

All AEs will be followed until they have abated, or until a stable situation has been reached. Depending on the event, follow up may require additional tests or medical procedures as indicated, and/or referral to the general physician or a medical specialist.

SAEs need to be reported till end of study within the Netherlands, as defined in the protocol

#### **9.5 Data Safety Monitoring Board (DSMB) / Safety Committee**

Not applicable

## 10. STATISTICAL ANALYSIS

The statistical analyses will be carried out by the investigator using SPSS software. Regarding descriptive statistics, numerical variables will be reported as mean  $\pm$ SD. Categorical variables will be reported as numbers and percentages. To test for normality of the data, Histogram and Kolmogorov-Smirnov test will be used. In case, of non-parametric data, the data will be transformed using natural logarithm. In general, a p-value  $<0.05$  will be considered statistically significant using two-tailed tests. In case of missing data, we will perform multiple imputation (MI) to estimate the missing value. MI is the process of replacing each missing data point with a set of  $m > 1$  plausible values to generate  $m$  complete data sets. Multiple imputation has been shown to produce valid statistical inference that reflects the uncertainty associated with the estimation of the missing data.

### 10.1 Primary study parameter(s)

We will be comparing the intervention group versus the placebo group regarding the change in insulin sensitivity as measured by the two-step hyperinsulinemic-euglycemic clamp. Changes in glucose disposal rate and infused glucose concentrations before and after the 12 week intervention period are our primary study parameters and will be analysed and compared between the two groups. Data from both groups will be analysed using a linear mixed model to include repeated measures. An intention-to-treat and per-protocol analysis will be conducted. Intervention and study period will be set as fixed factors, participants will be set as random factor. Age and sex will be added as covariates in the analysis.

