**Study design:** Double-blind randomized placebo-controlled trial using a potato-pectin fibre mixture versus a placebo (maltodextrin), against the background of a high-protein diet in all participants. Total duration: 12 weeks. A screening visit will be planned, eligibility will be determined and written informed consent will be obtained from participants, followed by two clinical investigation days (CID) to measure baseline characteristics. Afterwards, the dietary intervention trial starts. During the 12-week trial, 3 brief moments are planned to evaluate the trial and provide some additional data. After 12 weeks of intervention, two other CIDs are planned to measure endpoint outcomes. We will measure anthropometrics, insulin sensitivity,

energy harvesting and expenditure, substrate oxidation, body composition, gut permeability, microbiome composition and functionality, neurocognitive functioning, gene and protein expression in adipose and skeletal muscle tissue, physical activity, dietary intake and gastrointestinal complaints.

**Study population:** 44 overweight humans with impaired glucose homeostasis (male and female, age 30-75 years, BMI 28-40 kg/m^2, fasting glucose 5.6-6.9 mmol/l, HbA1c 42-47 mmol/mol), without any underlying diseases.

**Intervention:** Both groups will receive a high-protein diet (25% of energy intake (25E%)), along with either a potato-pectin fibre mixture or placebo (maltodextrin). Both dietary supplements will be taken three times daily for a total of 12 consecutive weeks.

**Main study parameters/endpoints:** The main endpoint is the change in tissue-specific insulin sensitivity, as measured by a two-step hyperinsulinemic-euglycemic clamp. Secondary outcomes are changes in energy and substrate metabolism (including production of SCFA and BCFAs), microbiome composition and functionality, gut permeability, brain health and inflammatory parameters.

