## 2. OBJECTIVES

### *Primary Objective:*

The main goal of this study is to provide evidence that steering saccharolytic/proteolytic fermentation by a specific indigestible fibre mixture supplemented against the background of a high-protein diet optimizes beneficial and minimizes detrimental substrate production. Most importantly, we will be looking into changes in peripheral insulin sensitivity.

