### *Secondary Objectives:*

Apart from determining possible effects on insulin sensitivity, we will also investigate the following parameters and analyse whether steering fermentation can influence the following secondary outcomes:

1. Hepatic and adipose tissue insulin sensitivity
2. Energy and substrate metabolism (energy harvest, energy intake, energy expenditure, fat and carbohydrate oxidation).
3. Circulating metabolites, inflammatory factors and blood lipid spectrum
4. Gut permeability
5. Brain health (neurocognitive functioning and food reward-related brain activity)
6. Adipose tissue and skeletal muscle metabolism
7. Composition and functionality of microbiome
8. Gastro-intestinal side-effects of provided dietary supplement against the background of a high-protein diet

Additionally, we will explore possible correlations in the gathered data, including anthropometric measurements, physical activity, dietary intake, glucose sensitivity, composition of gut microbiota, etc.

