## **8. METHODS**

### **8.1 Study parameters/endpoints**

#### **8.1.1 Main study parameter/endpoint**

The main endpoint is the difference in change in peripheral muscle insulin between intervention and control group, measured by hyperinsulinemic-euglycemic clamp.

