**8.3.10 Two-step hyperinsulinemic-euglycemic clamp**

To assess whole-body and tissue-specific insulin sensitivity, we will be performing a two-step hyperinsulinemic-euglycemic clamp, which is the gold standard to determine insulin sensitivity. The clamp will be performed on CID 2 and 4 and will take place after a >12h overnight fasting period and a standardized meal the evening before. Before starting the procedure, an intravenous canula will be inserted in an antecubital vein to provide intravenous access for insulin and glucose suppletion. Another intravenous canula will be inserted on the dorsal side of the contralateral hand to ensure intravenous access for blood sampling.

At  $t = 0$  minutes, a fasting blood sample (10ml) will be drawn, followed by infusion of a primed 6,6-H2-glucose tracer at 0.04mg/kg/min, which will be used to calculate endogenous glucose production (EGP), glucose appearance (Ra) and glucose disposal. Therefore, blood samples (6ml) will be drawn at  $t=90$ , 105 and 120 min. At  $t = 120$ min, insulin will be infused at a low,

constant rate of 10 mU/m^2/min for 3 hours to allow determination of hepatic glucose production. After 3 hours ( $t = 300\text{min}$ ), insulin infusion will be increased to 40 mU/m^2/min to inhibit EGP for 2.5 hours, providing insight in muscle insulin sensitivity. During insulin suppletion, plasma glucose levels will be measured every 5 minutes (1ml), upon which glucose (20% glucose solution) will be infused at 10-30ml/h to ensure a constant plasma glucose level of 4.8-5.2 mmol/l during the clamp. Afterwards, the total amount of infused glucose can be used to determine insulin sensitivity. Additional blood samples (6ml) will be drawn at  $t = 180, 240, 270, 285, 400, 420, 435$  and 450 minutes.

At  $t = 450\text{min}$ , insulin infusion will be terminated and glucose infusion will be slowly reduced to zero to ensure a safe normalisation of glucose homeostasis. Additional dietary supplements will be provided (sandwiches, drinks) to prevent a hypoglycemic state.

During the clamp, an indirect calorimetry will be performed, which will be described below.

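### Section 10.1 names two primary parameters, one misworded, for a trial sized on a single peripheral outcome, and the Summary and section 3 label the primary outcome differently

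*Protocol*

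**What the plan says.** The protocol describes its primary outcome in six places.

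- Summary: "The main endpoint is the change in tissue-specific insulin sensitivity, as measured by a two-step hyperinsulinemic-euglycemic clamp". Section 3 (Intervention period) uses the same tissue-specific label.
- Section 2, primary objective: "Most importantly, we will be looking into changes in peripheral insulin sensitivity".
- Section 4.4 sizes the trial on peripheral insulin sensitivity: a difference of 2.86 µmol/kg/min, alpha 0.05, 80% power, 22 per group.
- Section 8.1.1: "The main endpoint is the difference in change in peripheral muscle insulin between intervention and control group". The word sensitivity is missing.
- Section 10.1: "Changes in glucose disposal rate and infused glucose concentrations before and after the 12 week intervention period are our primary study parameters".

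The first secondary objective in section 2 is "Hepatic and adipose tissue insulin sensitivity", and section 8.1.2 repeats it among the secondary endpoints.

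Section 8.3.10 describes the clamp. A low-insulin step is used for hepatic glucose production. A high-insulin step, in which endogenous production is to be inhibited, is used for muscle insulin sensitivity. Glucose is given as a 20% solution at a varying rate, and "Afterwards, the total amount of infused glucose can be used to determine insulin sensitivity".

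The only multiplicity wording is in section 4.4. It treats the secondary outcomes as exploratory and applies Benjamini-Hochberg to the microbiome analysis. Section 10 sets p<0.05, two-tailed, in general.

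**The concern.** Three things do not fit together.

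1. Section 10.1 governs the test and has two primary parameters. The sample size has one outcome and spends the whole 0.05 on it. Nothing says whether either parameter suffices, both are needed, or one comes first.
2. Tissue-specific, in the Summary and section 3, is a wider label than peripheral. Section 8.3.15 says the clamp assesses peripheral, hepatic and adipose sensitivity, and two of those three are secondary elsewhere.
3. The concentration of the infused glucose is fixed by the preparation and cannot change between visits. As written, the second parameter cannot be analysed.

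At stake is whether a reader can tell, before the data are seen, which result answers the primary question and at what error rate. If the two clamp measures fall on opposite sides of 0.05, section 10.1 does not say what is concluded.

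**Working it through.** **The plan's own figure.** Inputs from section 4.4: post-measurement SD 3.95, pre-post correlation 0.73, difference 2.86, alpha 0.05 (two-tailed by section 10), power 80%, dropout 20%.

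- Residual SD = √(1 − 0.73²) × 3.95 = 2.70. This reproduces.
- n per arm = 2 × (1.96 + 0.84)² × (2.70/2.86)² ≈ 14.0, so 14; the t-test version gives 16. Dividing by 0.8 gives 18 or 20 per arm, not 22.
- With the change-score SD from the same inputs, √(2 × (1 − 0.73)) × 3.95 = 2.90, n ≈ 16.2, so 17, and 17/0.8 = 21.25, so 22 per arm. N = 44 reproduces on the normal approximation (t-test: 18, then 23 per arm).

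The stated 44 is therefore on the safe side for SD 2.70 and matches a change-score analysis. Either way it is a calculation for one outcome with the full 0.05. With 17 to 18 evaluable per arm (22 less 20%), t-test power for that outcome is 85-87% at SD 2.70 and 80-82% at SD 2.90.

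**Reading the second parameter.** Taken literally, the infusate concentration is constant and gives no test. Section 8.3.10 works with the amount infused, so the sensible reading is infusion rate or amount. The figures below use that reading.

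**If either parameter may declare success.** For two two-sided tests at 0.05, the error rate is 0.05 + 0.05 − P(both reject). Independence gives the maximum, 1 − 0.95² = 0.0975. The protocol gives no correlation, so these are assumed values under a bivariate normal:

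| Assumed correlation | P(both reject) | Type I error |
|---|---|---|
| 0 | 0.0025 | 9.75% |
| 0.7 | 0.0165 | 8.35% |
| 0.8 | 0.0219 | 7.81% |
| 0.9 | 0.0296 | 7.04% |
| 0.95 | 0.0354 | 6.46% |

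**If both are required.** Type I error cannot exceed 5%, because each test alone is held at 5%. Power falls. As an illustration, suppose each parameter alone has 80% power. Joint power is 0.8 × 0.8 = 64% at correlation 0, and about 71%, 75% and 76% at correlations 0.7, 0.9 and 0.95 (bivariate normal, each test statistic with mean 1.96 + 0.84 = 2.80).

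**If alpha were split.** At 0.025 each, SD 2.70 and 17 to 18 evaluable per arm, power per parameter is 77-79%, just under the stated 80%. Restoring 80% needs 19 evaluable per arm, or 24 randomised (19/0.8 = 23.75), N = 48. This assumes that the second parameter has the same standardised effect.

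**With one named primary.** Type I error is 5% and the section 4.4 calculation applies as it stands.

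**The case against.** The best defence is that the intention is clear. Sections 2, 4.4 and 8.1.1 all point to peripheral insulin sensitivity, the sample size uses that one outcome in one unit, and hepatic and adipose sensitivity are twice listed as secondary. This stands as to the construct. It does not settle the variable: section 10.1 offers two measures and ties neither to a clamp step.

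It can also be said that the two measures are nearly the same thing. In the high-insulin step endogenous production is meant to be suppressed, so infusion rate and disposal should track closely. That is why the correlated rows of the table matter more than 9.75%. It reduces the inflation without removing it.

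A reader might infer more than the documents support:

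- *Three tissues are three primaries.* The Summary and section 3 do not list three tissues as primary, and sections 2, 4.4 and 8.1.2 make the other two secondary and exploratory. An error rate for three tissue tests has no basis here.
- *A constant primary also inflates error.* A quantity that cannot vary gives no false positives. The inflation exists only under the corrected reading.
- *The total infused pools both clamp steps.* Section 8.3.10 does not say it is summed across steps. It is unspecified, no more.
- *Two analysis sets add further routes to success.* Section 10.1 says "An intention-to-treat and per-protocol analysis will be conducted", which is neither wrong nor contradictory. Which set decides is commonly left to the statistical analysis plan, which is not at hand.

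A separate analysis plan could add a decision rule. It would not remove the conflicting definitions from the protocol.

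**Conclusion.** The point holds as a should-fix. Section 10.1 names two primary parameters without a decision rule, for a trial sized on one. One of them is misworded, and the Summary and section 3 carry a wider label than the objectives, sample size and endpoint sections.

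If either parameter suffices, type I error is about 6.5% to 8.4% at assumed correlations of 0.95 to 0.7, with 9.75% as the ceiling. If both are required, error is controlled and power is lost. The protocol does not say which applies, so neither outcome can be stated as fact. Saying that nothing decides the trial would go too far: the peripheral construct is recoverable from three sections, and the inflation is modest if the two measures agree closely.

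**What to change.** Name one primary variable for peripheral insulin sensitivity and use it in identical words in the Summary and sections 2, 3, 4.4, 8.1.1 and 10.1. One candidate is the between-group difference in change in glucose disposal rate (µmol/kg/min) during the high-insulin step, which section 8.3.10 already assigns to muscle. In section 10.1, replace *infused glucose concentrations* with *glucose infusion rate* and make it a secondary parameter. Restore the missing word in section 8.1.1. Keep hepatic and adipose sensitivity secondary.

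The steady-state window and the deciding analysis set can be left to the statistical analysis plan.

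The cost is a wording amendment. No added measurement, participant or sample size is needed, and the single 0.05 in section 4.4 then applies to the one test it was calculated for.

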#### 4.4 Sample size calculation

We used G-power to calculate the sample size required to detect a clinically relevant change in peripheral insulin sensitivity.

To calculate the sample size, we used the data derived from previous clinical trials of our research group using a comparable participant population to assess effects of alterations of the gut microbiota on peripheral insulin sensitivity with the hyperinsulinemic-euglycemic clamp technique. Based on the studies' data we calculated a within-group residual SD of 2.70, which was based on a SD of post measurement of 3.95 and a pre-post correlation of 0.73;  $\sqrt{(1-0.732)} \times 3.95 = 2.70$ . Twenty-two (we aim to include an equal number of males and females: 11

males and 11 females) participants per group (N = 44) are needed to detect a physiological relevant difference of 20% (2.86µmol/kg/min) in the change in our primary outcome parameter peripheral insulin sensitivity measured via the hyperinsulinemic-euglycemic clamp technique, assuming a power of 80%, an  $\alpha$ -value of .05, a within-group residual SD of 2.70 and a 20% dropout rate. The described secondary outcomes will be analysed exploratively, for microbiome analysis Benjamini-Hochberg procedure will be used to prevent false-positive results.

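### The terms listed for the primary mixed model include no intervention-by-period term and no baseline value, and no primary contrast is named, so the model does not match the difference-in-change endpoint or the SD used for sizing

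*Protocol*

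**What the plan says.** Section 8.1.1 defines the main endpoint as the "difference in change in peripheral muscle insulin between intervention and control group", measured by clamp. Section 8.3.10 schedules the clamp twice, on CID 2 and CID 4, so each participant contributes one value before and one after the intervention.

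Section 10.1 opens by saying that the groups are compared on the change in insulin sensitivity. It then chooses a linear mixed model and lists its terms: "Intervention and study period will be set as fixed factors, participants will be set as random factor". The covariates follow: "Age and sex will be added as covariates in the analysis". No product of intervention and period is listed, baseline insulin sensitivity is not a covariate, and no coefficient or contrast is named as the primary test.

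Section 4.4 sizes the trial on "a within-group residual SD of 2.70, which was based on a SD of post measurement of 3.95 and a pre-post correlation of 0.73". The target is a difference of 2.86 µmol/kg/min with 80% power, 22 participants per group and 20% dropout. Section 10 states that results "will be considered statistically significant using two-tailed tests".

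**The concern.** Three statements should describe the same analysis and do not. The endpoint is a difference in change. The sizing SD is the residual SD after regression on baseline. The listed model has neither the term that carries a difference in change nor the covariate that yields that residual SD.

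With group and period as the only fixed factors besides age and sex, the group coefficient is the between-group difference averaged over the two clamps. Randomisation makes the expected difference at baseline zero, so the average is half the week-12 effect. It also keeps the stable between-person variation that a change or baseline-adjusted analysis removes. A literal run would therefore report about half the true effect with a larger standard error.

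Age and sex do not repair this. They are constant within a participant, so with complete pre/post pairs they cancel out of the difference in change. Section 10.2 extends the same methods to the secondary endpoints, so the gap is not confined to one analysis.

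**Working it through.** **Inputs.** From section 4.4: post SD 3.95, pre-post correlation r = 0.73, difference 2.86, 22 per group, 20% dropout (22 × 0.8 = 17.6 completers per group), alpha 0.05. Two-sided testing is from section 10. The baseline SD is not given; I assume 3.95 and then vary it from 3.0 to 5.0. Power is for a two-sample t test (noncentral t) unless stated.

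**Step 1: the plan's own figures.** Residual SD = √(1 − 0.73²) × 3.95 = 2.70, as stated. (The formula shows 0.732 in the text at hand; the result of 2.70 shows that 0.73 squared is meant.)

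Sample size by normal approximation, n = 2(1.96 + 0.842)² × SD²/2.86²:

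- SD 2.70: 13.99, so 14 per group, and 14/0.8 = 17.5, so 18. The t test needs 16, giving 20.
- SD of change, √(2 × (1 − 0.73)) × 3.95 = 2.90: 16.2, so 17 per group, and 17/0.8 = 21.25, so 22. The t test needs 18, giving 23.

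The stated 22 is thus more than the stated SD requires, and equals the normal-approximation figure for a change analysis.

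**Step 2: the listed terms, with intervention as a between-group factor.** The coefficient compares participants' pre/post means.

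- Expected value: (0 + 2.86)/2 = 1.43.
- SD of a participant's mean: 3.95 × √((1 + 0.73)/2) = 3.67.
- Standardised effect: 1.43/3.67 = 0.39.

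**Step 3: the two analyses that match the endpoint.**

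- Intervention-by-period (change): 2.86/2.90 = 0.99.
- Baseline-adjusted week 12: 2.86/2.70 = 1.06.

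| Analysis | Estimates | SD | Power, 17.6 per arm | 18 per arm | 22 per arm |
|---|---|---|---|---|---|
| Listed terms, between-group coefficient | 1.43 | 3.67 | 20% | 21% | 24% |
| Intervention-by-period | 2.86 | 2.90 | 81% | 82% | 89% |
| Baseline-adjusted | 2.86 | 2.70 | 86% | 87% | 93% |

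Simulated mixed models (18 per group, 300 replicates) agree: mean estimate 1.33 and power 19% for the listed terms; 2.90 and 82% with the interaction.

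**Step 4: sensitivity to the assumed baseline SD (b).** The SD of the mean is ½√(b² + 3.95² + 2 × 0.73 × 3.95b), and the SD of change is √(b² + 3.95² − 2 × 0.73 × 3.95b). Power at 17.6 per arm:

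| b | SD of mean | Listed terms | SD of change | Intervention-by-period |
|---|---|---|---|---|
| 3.0 | 3.24 | 25% | 2.70 | 86% |
| 3.95 | 3.67 | 20% | 2.90 | 81% |
| 5.0 | 4.17 | 17% | 3.43 | 67% |

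The baseline-adjusted figure does not move, because its residual SD depends only on the post SD and the correlation.

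**Step 5: help from age and sex under the literal reading.** If they explained 10% to 30% of the variance (an assumption), power for the listed terms would be 22% to 27% at 17.6 per arm and 27% to 33% at 22.

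**The case against.** The strongest reply is that the absence of an interaction is inferred from silence. Section 10.1 says which variables are fixed factors. It does not restrict the model to main effects, and it does not name the intervention coefficient as the test. Its opening sentence commits to comparing change between groups, and an analyst guided by it might well add the interaction. This stands, and it is why the 20% must be labelled as the outcome of one reading.

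Nor does a two-term model force the half effect. If intervention is coded as on-treatment, zero for everyone at baseline, the same two terms recover the full effect (simulated mean 2.87, power 86% at 18 per group). This also stands, although the protocol describes intervention and placebo as parallel groups, which makes a between-group factor the more natural reading.

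The power figures rest on an unstated baseline SD, hence the range. Section 8.5 allows withdrawn participants to be replaced, so 22 completers per arm is possible and 24% may apply. The cancellation of age and sex is shown only for complete pairs; with dropout and multiple imputation it need not be exact.

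Finally, model terms are often left to a statistical analysis plan, which is not at hand. That carries less weight here: the protocol does not defer the model but lists its fixed factors, random factor and covariates, and that list does not fit its own endpoint.

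**Conclusion.** The mismatch is real. The terms in 10.1 do not carry the endpoint in 8.1.1, do not produce the SD in 4.4, and leave the primary contrast unnamed. Depending on how the sentence is implemented, power at 17.6 to 18 completers per arm is about 20%, 81-82% or 86-87%, and the quantity estimated is 1.43 or 2.86. These figures assume a baseline SD of 3.95.

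A reader might infer two stronger conclusions that the protocol does not support:

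- That the trial has only 20% power for its primary test. The protocol names no such test, and its stated intention is to compare change.
- That the sample size is too small. Under the equal-SD assumption both matching analyses exceed 80% power after 20% dropout, so N = 44 need not change. The baseline-adjusted analysis keeps 86% whatever the baseline SD. The change analysis would fall below 80% if the baseline SD were well above 3.95, which favours the adjusted form.

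**What to change.** In section 10.1, name the primary test as the week-12 difference between groups in peripheral insulin sensitivity, from a model adjusted for the baseline clamp value and the minimisation factors in section 8.2 (age, sex and BMI). Equivalently, use a repeated-measures model with the group means constrained equal at baseline, and test the group difference at week 12. Either form matches the residual SD in section 4.4.

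At minimum, keep the present model, add the intervention-by-period term and name it as the primary contrast. That restores the endpoint but not the precision from baseline adjustment.

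For secondary endpoints also measured mid-trial, such as the week 6 blood samples and the mid-trial stool samples, keep the repeated-measures model with baseline adjustment and a group-by-visit term. A week-12-only ANCOVA would leave the intermediate visits unused.

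The cost is one paragraph of wording. The baseline clamp is already scheduled for every participant, so no new data and no change in sample size are needed. The wording should be settled before unblinding.
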